## Abstract

Plantar fasciitis is generally described as an inflammation of the plantar fascia and adjacent tissues around calcaneus tuberosity. Plantar fasciitis onset has been proposed to have an internal mechanical cause, even though this is inadequately recognized. Studies related to alternation in lower-extremity biomechanics that leads to reduced domes of the foot are hypothesized to cause tension in the underlying fascia. Similarly, despite a wealth of anecdotal data suggesting a direct connection between foot mechanism and disability. This condition typically leads to calf muscular stiffness, soreness in the bottom of the feet, decreased range and foot function, strength, and balance impairment. These results in interference with the normal biomechanics of ambulation. A total of (n=66) individuals with plantar fasciitis will be selected for the trial. Subjects will be allocated to Groups A and B at equal allocation with randomization. Group A will undergo foot core exercises, while Group B will undergo ankle proprioceptive neuromuscular facilitation, with both groups receiving conventional treatment. The regimen lasts for 40 minutes, 5 days, for 6 weeks. The outcome measures will be assessed on Foot Functional Index, modified Star Excursion Balance Test (mSEBT), Visual Analogue Scale (VAS), and Weight Bearing Lunge Test (WBLT) be assessed at the initiation and completion of the entire treatment protocol. Prior and after therapeutic intervention results will be analyzed. Based on the comparison of the two treatments' effects on measuring outcomes in individuals with plantar fasciitis, an analysis will be conducted.

## Introduction

The ankle and foot are constituted of twenty-six separate small bones as well as the major bones of the leg.
^
1
^ The ankle joint creates a connection that enables the lower extremity to connect with the foot.
^
1
^ Ankle and foot mobility is described in the following three categorical planes: longitudinal, coronal, and axial.
^
2
^ The sole of the foot comprises three main vaults: a transverse arch, and two longitudinal arches. The muscles, ligaments, tendons, and fascia in the foot support these domes.
^
3
^ The gastrocnemius and soleus muscles work together to predominantly plantarflex the ankle.
^
4
^ The plantar layers contain the intrinsic foot muscles in their anatomical alignment.
^
4
^ The ends of extrinsic foot muscles are connected at the foot distally and the leg proximally, respectively.
^
5
^ A broad, longitudinally oriented strand that are firmly linked to the sole of the foot is referred to as plantar fascia. The proximally plantar fascia is attached to the calcaneal tuberosity and distally split into five bands for each toe.
^
6
^

A gradual degenerative irritation of the plantar fascia, which starts at the medial calcaneal tuberosity, as well as the nearby perifascial tissues, results in plantar fasciitis, an inflammatory disorder. The plantar fascia serves a crucial role in accurate foot mechanics.
^
7
^ The main prevalent source of heel discomfort is plantar fasciitis. This is responsible for around 15% of all foot issues brought to the attention of healthcare practitioners.
^
8
^ A mechanical model known as the “windlass mechanism” offers a complete justification for the biomechanical components of the foot. Such knowledge is crucial for clinical practice since it could give medical experts a comprehensive grasp of the connection between pathologies and biomechanical factors.
^
9
^ A history of pain with the first steps in the morning, pain that becomes worse with loading activities and gets better over the day, and palpable soreness in the medial calcaneal tubercle are used to make the diagnosis of this illness. Achilles tendon tightness may cause patients to have decreased ankle dorsiflexion, which might lead to anticipatory overpronation of the ankle.
^
10
^

Theories of Proprioceptive Neuromuscular Facilitation (PNF) may be beneficial in enhancing postural balance and stability. In the development of a therapeutic relationship, PNF is characterized as a strategy to improve the neuromuscular stimulation of the proprioceptive sense response mechanism. This technique set contains methods that stimulate proprioceptive sense to improve the response of the neurological and muscular systems. PNF is a stretching method that is utilized in the realms of exercise and sports to increase muscular flexibility, strength, and balance as well as joint mobility.
^
11
^ The technique emphasis of timing in ankle proprioceptive neuromuscular facilitation (PNF) was enhanced to synchronise and strengthen the movement patterns of both the foot's intrinsic and exterior muscles.
^
12
^

Exercises for the foot core were done to maintain proper foot alignment, manage the position of the arch, and activate the proprioceptors on the foot's sole to enhance balance. As a result, earlier gait retraining studies have started to include foot core exercise to lower the risk of injury in individuals when the striking pattern abruptly changes. The towel curls, foot doming, and toe spread, which have been shown to be efficient treatments to develop the arch muscles, might be used to strengthen the foot muscles in order to stabilise the form of the arch.
^
13
^

Visual analogue scale (VAS) is used to assess the pain, rated from zero to ten. The foot functional index (FFI) questionnaire evaluates physical discomfort, impairments, as well as activity-restricting foot pathologies in everyday functioning.
^
14
^ The 23 items on the questionnaire are categorized into three subdimensions: pain, activity limitations, and disabilities. It was created in English, and it has official translations for usage in Chinese, German, French, Italian, and Spanish. Because standardisation is crucial when utilising measures of assessment, checklists created in other languages must be translated and their parametric qualities assessed to promote comparability between research.
^
15
^ Ankle dorsiflexion may be directly monitored with weight bearing lung test. The therapist measured the amount of dorsiflexion in affected limbs while the patient will be in a lunge position. The therapists either employed an inclinometer or a measuring tape to evaluate the numerical outcome. In several disorders, including patellofemoral pain syndrome and overpronation of the foot, which may result in plantar fasciitis, it is well-accepted that inadequate ankle dorsiflexion plays a vital role.
^
16
^

The modified Star Excursion Balance Test is among the popular techniques for the clinical examination of dynamic balance (mSEBT). When assessing the likelihood of lower extremity injuries, clinicians frequently employ just one of these diagnostic techniques and one outcome factor. It is well-established that age, sex, and sport may affect dynamic balance scores.
^
17
^

The purpose of the study is to compare the effects of foot core exercises and ankle proprioceptive neuromuscular facilitation on pain, range of motion, and dynamic balance in patients with plantar fasciitis. The plantar fascia is subjected to steadily increasing loading stress if these musculatures are weaker and the plantar fascia lacks flexibility, which flattens the longitudinal arch and causes foot eversion. This results in the hip of the afflicted side descending, which causes the hip to rotate inward, and a reduction in the medial joint space of the knee. This may result in plantar fascia overload, muscle imbalance, abnormal gait, and reduced functional performance. Foot core exercises and Proprioceptive neuromuscular facilitation have been shown to be helpful in the reduction of pain, restoring the motion, and regaining muscular strength. There is a lack of literature that emphasizes a comparison between foot core exercises and PNF that helps in improving dynamic state of balance, as well as functional status in patients suffering from plantar fasciitis. As a result, strong evidence is very important in this field.

## Aim and objective

1)To assess and evaluate the effects of foot core exercises on pain (VAS and FFI), range of motion (WBLT), and dynamic balance (mSEBT) in patients with plantar fasciitis.2)To assess and evaluate the effects of ankle proprioceptive neuromuscular facilitation on pain (VAS and FFI), range of motion (WBLT), and dynamic balance (mSEBT) in patients with plantar fasciitis.3)To compare the effects of foot core exercises and ankle proprioceptive neuromuscular facilitation on pain (VAS and FFI), range of motion (WBLT), and dynamic balance (mSEBT) in patients with plantar fasciitis.

**Trial Design:** single centric two arm parallel, comparative open labelled superiority trial.

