### Analysis

All the results will be calculated using SPSS 27 version. Demographic variables (Confounding factors) as per quantitative assessment will be resulted for finding observational values on mean Standard deviation minimum and maximum. Quantitative assessment will be observed on frequency and percentage. The data for inferential statistics, with outcome variables will be tested for normality using Kolmogorov Smirnov Test. A parametric test will be used if the data follows normal distribution. Non-normal data will be attempted for transformation to normality by using mathematical algorithm such as log or exponential function or box cox method. For finding the significance over the mean pre- and post T-paired will be used for analysis if data still persist with non-normal distribution alternative Wilcoxon test will be used for finding the difference for mean significance between the two groups (Inter) un-paired t-test will be used while the Man-Whitney will be used as an alternative t-test for non-normal data Association and analysis for finding the significance of confounding parameters will be evaluated using Chi square test or Fischer Exact Test or using multi-variant analysis.

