### Primary outcome

The two groups will be compared using inferential statistics for their mean change in the primary variable (Foot functional index and modified star excursion test) between baseline and six weeks. For research participants, random effects will be generalised, treatment group and visit count will be taken into consideration while analysing fixed effects. At the conclusion of the intervention, the effect size over the mean change difference on the primary variable will be assessed and the matching 95% confidence interval (CI) given.

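### Objectives 1 and 2 ask for the effect of each exercise separately, but no arm lacks exercise and the only analysis that could address them is a within-arm pre-post test

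*Protocol article*

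**What the plan says.** The section Aim and objective lists three objectives. The first is "To assess and evaluate the effects of foot core exercises on pain (VAS and FFI), range of motion (WBLT), and dynamic balance (mSEBT"), and the second is "To assess and evaluate the effects of ankle proprioceptive neuromuscular facilitation on pain (VAS and FFI), range of motion (WBLT), and dynamic balance (mSEBT"). Each concerns one exercise alone and names nothing to compare it with. Only the third is a contrast: "To compare the effects of foot core exercises and ankle proprioceptive neuromuscular facilitation on pain" and the other outcomes. The same section calls the design a "single centric two arm parallel, comparative open labelled superiority trial".

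Both arms receive an exercise programme. The Abstract has them "with both groups receiving conventional treatment", and the Intervention section allots 10 of each 40-minute session to conventional therapy in each group. For Group A it specifies ultrasound with plantar fascia and Achilles stretching. Outcomes are measured at baseline and at six weeks.

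The Analysis section plans two kinds of test. Within a group: "For finding the significance over the mean pre- and post T-paired will be used for analysis", with Wilcoxon as the alternative. Between groups: "difference for mean significance between the two groups (Inter) un-paired t-test will be used", with Mann-Whitney as the alternative. The Primary outcome section then states: "The two groups will be compared using inferential statistics for their mean change in the primary variable". Nothing in the article limits the within-group results to description.

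**The concern.** An effect of foot core exercises, or of PNF, is a contrast between having the exercise and not having it. The trial has no arm without exercise, so it does not contain that contrast for either one. What it does contain is each arm's change over six weeks, together with a significance test of that change. Read in order, the objectives and the Analysis section invite the report to treat a significant paired test as evidence that the exercise worked.

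Two of the three stated objectives could then end in efficacy statements that the design cannot support. The risk is greatest if the arms turn out not to differ: two significant paired tests could be presented as two effective treatments, although the same data would fit two exercises that add nothing to conventional therapy and time.

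**Working it through.** **1. Which contrast could answer each objective?**

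| Objective | Contrast needed | Available in the design? |
|---|---|---|
| 1. Effect of foot core exercises | Foot core + conventional vs conventional alone (or no treatment) | No such arm |
| 2. Effect of ankle PNF | PNF + conventional vs conventional alone (or no treatment) | No such arm |
| 3. Foot core vs PNF | Group A vs Group B on a common background | Yes, randomised |

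For objectives 1 and 2 this leaves only the pre-post change within an arm. The article does not itself tie the paired test to these objectives. The link is inferred: it is the only within-arm test planned, and no other contrast in the design could serve.

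**2. What does within-arm change contain?**

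Change = exercise + conventional therapy + natural course + regression to the mean + non-specific effects of attending.

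- *Conventional therapy*: given with the exercise, so it cannot be separated from it. The article's own planning figure has this form: the FFI change of 13.01 is for foot core exercises with conventional physiotherapy, that is, for the package.
- *Natural course*: patients enter with at least three months of heel pain and are measured twice, six weeks apart.
- *Regression to the mean*: plausible for pain, because entry requires painful symptoms. It is weaker for range of motion and balance, since no entry criterion selects on the lunge or balance test.

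The opening text of the Protocol section mentions conventional therapy for Group A only, whereas the Abstract and the Intervention section give it to both groups. These passages must be reconciled. The point holds either way, because natural course and non-specific change remain in both arms.

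**3. Inputs for an illustration (FFI only, from Sample size calculation)**

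- Two-sided alpha 0.05 (z = 1.96); power 80% (z = 0.84).
- SD of change 3.24; between-group difference to detect 2.602.
- n = 25 per group before dropout, 33 after.
- Post-treatment SD 10.69. This is not an SD of change and is used only as a sensitivity value.

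**4. The plan's own figure**

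n = 2 × (1.96 + 0.84)² × 3.24² / 2.602² = 24.31, rounded up to 25 per group. The stated figure reproduces. It is sized on a between-group difference, that is, on objective 3.

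**5. How often is the paired test significant if the exercise adds nothing?**

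*Assumption*: an average improvement of d points arises from causes other than the exercise. The documents give no value for d, so a range is shown.

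Noncentrality = d / (SD / √n). With n = 25 (24 df), the two-sided critical t is 2.06.

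- d = 2, SD 3.24: 2 / (3.24/5) = 3.09; probability of significance 84%.
- d = 2, SD 10.69: 2 / (10.69/5) = 0.94; probability 15%.

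| Assumed non-exercise change | SD 3.24, n = 25 | SD 10.69, n = 25 |
|---|---|---|
| 1.3 points (10% of 13.01) | 49% | 9% |
| 2.0 points | 84% | 15% |
| 2.6 points (20%) | 97% | 22% |
| 6.5 points (50%) | over 99.9% | 83% |

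With n = 33 and SD 3.24, the 2-point figure is 93%.

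The frequency of a misleading p-value depends heavily on d and on the SD. The reason it misleads does not: under either SD the test asks whether mean change is zero, and not whether the exercise caused it.

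**The case against.** The strongest reply is that the trial's inferential structure is already between-group. It is labelled a comparative superiority trial, its stated purpose is to compare the two exercises, the sample size rests on a between-group difference, and the primary analysis compares mean change between arms with an effect size and 95% CI. This stands in full. It confines the point to the wording and interpretation of two objectives.

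It can also be said that a paired test is a valid test of whether mean change is zero, so listing one is no error. That stands too. The fault is in calling the result the effect of the exercise, which is why dropping within-group p-values is a matter of reporting preference.

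Two stronger readings are tempting, and the documents do not support them.

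- A reader might infer that the paired tests are almost certain to be significant whatever the exercises do. The full 13.01-point change does give a large paired t (20.1 with SD 3.24, 6.1 with SD 10.69, n = 25), but that change belongs to the whole package and says nothing about a case where the exercise is inert. For that case the size of the change is unknown, and the illustration runs from 9% to over 99.9%. There are no corresponding figures for the pain scale, the lunge test or the balance test.
- A reader might infer that significance in one arm and not in the other will be taken as a difference between arms. Nothing in the article proposes this, and it specifies a direct between-group test.

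The reply that the matter can wait for a statistical analysis plan fails. The objectives and the paired test are both stated here, and no analysis plan can supply a comparator that the design lacks.

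**Conclusion.** The point holds as a mismatch between two of the three objectives and the design. Objectives 1 and 2 ask for the separate effect of each exercise. The trial can deliver only each arm's change under exercise plus conventional therapy, and that cannot be attributed to the exercise.

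Objective 3, the primary analysis and the sample size are not touched by this. What objective 3 estimates is foot core against PNF, and not the effect of either one alone.

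No single figure measures the defect. For FFI, an assumed 2-point improvement unrelated to the exercise would give a significant paired test about 84% of the time (SD 3.24) or about 15% (SD 10.69) with 25 per arm. The conclusion does not depend on these figures. It rests on the absence of an arm without exercise, which is explicit, and on the inferred but reasonable reading that the paired test is meant to serve objectives 1 and 2. It merits correction before the trial starts, because it changes what the trial may conclude.

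**What to change.** - Reword objectives 1 and 2 as describing the change from baseline to six weeks in each group, under exercise plus conventional therapy, for each outcome.
- In the Analysis section, report within-group results as mean change with 95% CI. Within-group p-values are optional.
- Add a sentence that no conclusion about efficacy will be drawn from within-group change, and that inference on treatment effect rests on the between-group difference in objective 3.

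The cost is a rewording of two objectives and a small change to the Analysis section, with no added arm, visit or patient. The article says the study has yet to start, so the change can precede any data. The downside is two less ambitious objectives. Keeping them as worded would need an arm with conventional therapy alone, which is a different and larger trial.

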## Protocol

The study will be conducted at Musculoskeletal Physiotherapy OPD of Acharya Vinoba Bhave Rural Hospital and Musculoskeletal Physiotherapy OPD of Ravi Nair Physiotherapy college, Sawangi (Meghe) Wardha, after receiving approval from ethical committee of Datta Meghe Institute of Higher Education and Research. The participants diagnosed as plantar fasciitis and follows the inclusion criteria will be randomly selected using simple random sampling and divided into Group A and Group B using computer generated list. After explaining the study protocol in detail, written consent will be signed by the participants. The duration of study will be one year. A total of 33 participants will be in each group. The outcome measures are foot functional index, modified star excursion balance test, weight bearing lunge test and visual analogue scale used to assessed pain, range of motion, dynamic balance, disability, and limitations in activities of daily living. Group A patients will be receiving foot core exercises and conventional therapy and group B patients will be receiving ankle proprioceptive neuromuscular facilitation. The outcome measure will be assessed at the base line and after six weeks of intervention
Figure 1. Explains the study procedure.

**Figure 1. f1:**
[figure not shown]
Study procedure flow chart.

### Inclusion criteria

1)A progressive onset of heel pain lasting three months or more, localized to the medial calcaneal tubercle.2)Sharp and worsen pain with the first few steps out of bed in morning.3)Positive windlass test.4)Both male and female.5)Age ranging between 40-60.

### Exclusion criteria

1)Patients with type 1 or 2 Diabetes Mellitus, systemic inflammatory arthritis, cancer, active tuberculosis.2)Arthrosis of the ankle, knee, and hip.3)Pregnant women.4)Patients with numbness or tingling with or without provocation in the lower extremity, undiagnosed pain.5)Patients currently receiving treatment and using steroids within the last six months for the plantar fasciitis.

### Intervention

**Control group**

Group A will be given foot core exercises which includes heel raise, toe curls, foot doming, toe spreading, balancing board, and tennis ball roll under foot along with conventional therapy which includes ultrasound, plantar fascia stretching and Achilles stretching. The foot core exercises mentioned in
Table 1. which lasts for 30 mins with 10 mins of conventional therapy. The entire protocol lasts for 40 min, five days a week, for six weeks.

**Table 1. T1:** Foot core exercises.

Foot core exercises	1-2 weeks	3-4 weeks	5-6 weeks
Double Leg Heel Raise	1 × 10 times	2 × 10 times	2 × 15 times
Single Leg Heel Raise	1 × 10 times	2 × 10 times	2 × 15 times
Towel curls	3 × 10 times	3 × 20 times	3 × 10 times (+0.25 kg)
Foot doming	2 × 10 times	2 × 15 times	2 × 20 times
Toe spread	2 × 10 times	2 × 15 times	2 × 20 times
Balance board	2 × 20 second	2 × 25 second	2 × 30 second
Foot relaxes	1 × 30 second	1 × 30 second	1 × 30 second

**Experimental group**

Group B will be given Ankle Proprioceptive Neuromuscular Facilitation (PNF) which includes techniques such as slow reversal (SR), and rhythmic stabilization (RS) along with conventional therapy. The PNF protocol mentioned in
Table 2 which last for 30 mins with 10 mins of conventional therapy. The entire protocol lasts for 40 min, five days a week, for six weeks.

**Table 2. T2:** Ankle PNF technique.

Muscles	PNF technique	Duration (sec) of technique	Repetition of each technique
Ankle Plantarflexors	Slow Reversal	35	3
	Rhythmic Stabilization	90	3
Ankle Dorsiflexors	Slow Reversal	35	3
	Rhythmic Stabilization	90	3
Ankle Invertors	Slow Reversal	35	3
	Rhythmic Stabilization	90	3
Ankle Evertors	Slow Reversal	35	3
	Rhythmic Stabilization	90	3

Legends: proprioceptive neuromuscular facilitation.

